### Subjects

Participants will be selected from among patients with knee pathology who have undergone surgery, following a physiotherapy appointment.

### Inclusion and exclusion criteria

The inclusion criteria are as follows: (i) patients that are aged 18 or over; (ii) that consent to take part in the study; (iii) that can read and write; and (iv) have undergone knee surgery. The exclusion criteria are: patients with permanent or temporary dysfunctions of the central or peripheral nervous system; that have or have had previous surgeries on the ipsilateral knee; unconsolidated fractures; partial or total amputation of the upper or lower limbs.

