**Table utbl0001:** 

Subject area:	Medicine and Dentistry
More specific subject area:	Rehabilitation; Health policies and research in health services.
Name of your protocol:	PROM_R
Reagents/tools:	EQ-5D-5L - EuroQol 5 Dimensions HADS - Hospital Anxiety and Depression Scale BREQ2 - Behavioural Regulations in Exercise Questionnaire
Experimental design:	An experimental study with 75 selected participants. Protocol that includes rehabilitation intervention in adults with an experimental group and a control group, enrolled in rehabilitation institutions located in rural and urban regions, carried out by the physiotherapist. Performance at the beginning of the program will be measured and then compared with performance after the supervised intervention in both groups. Participants will be included in the intervention after agreeing to take part in the study.
Trial registration:	Study protocol was registered in Clinicaltrials.gov with the number NCT06206018.
Ethics:	The study protocol was submitted to the Ethics Committee of the Nacional School of Public Health – NOVA University of Lisbon and was approved (CEENSP n°3/2022).
Value of the Protocol:	- The protocol is important for evaluating the effects of a structured four-week rehabilitation program on the quality of life reported by participants after knee injury, and who live in rural or urban regions. - There is a lack of knowledge about the selection of Patient-Reported Outcomes Measures (PROMs) considering the different domains envisaged by patients with knee pathology when participating in rehabilitation programs. - This article will contribute recommendations for a rehabilitation program based on supervised physical exercise after knee injury.

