## Description of protocol

Different musculoskeletal conditions affect people all over the world and were considered by the WHO to be the main cause of disability in 4 of its 6 regions; they cause an increase in the associated burden with a real impact on our society. One of these conditions is related to the knee, which is associated with complex and vulnerable injuries, the most common of which are caused by ligaments, menisci, and cartilage. Structured rehabilitation programs are essential as they improve quality of life by optimizing proprioception, strength, and muscle function, which can be compromised immediately after surgery as a consequence of reflex inhibition of motor neurons and immobilization [1].

The aim of this experimental clinical study is to analyze the effects of a 4-week supervised rehabilitation program on the quality of life reported by participants after knee surgery. As a secondary objective, we intend to analyze the impact that the program has on the level of anxiety and motivation to practice exercise through the application of PROMs, in patients who have undergone knee surgery.

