### Sample size calculation

GPower@ software was used to calculate the sample size, determining a minimum of 60 patients assuming an alpha error of 0.05, a sample power of 0,5 (Power = 1-β err prob), and an effect size of 0,5. Anticipating a potential loss of 20% in follow-up due to the period required for the program (with evaluation at 6 months) and based on the numbers from each of the centers, a total of 75 patients will be recruited.

The experimental group will complete the rehabilitation program, in which the intervention takes place in five sessions per week over 4 weeks, with the physiotherapist supervising all the sessions (Fig. 1).

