## Statistical methods

The Statistical Package for Social Sciences (SPSS®) 29 software (IBM Corp, Armonk, New York, USA) will be used. Different statistical procedures will be used to analyze the data, including descriptive and inferential techniques. Non-parametric tests, Chi-square and Mann-Whitney U will be used when the normality of the distribution is not verified. If normality or small deviations allow the use of parametric tests, we will apply the Student's *t*-test for independent measures.

The differences between the groups at the different assessment times will be calculated using a two-factor ANOVA. A Multiple Linear Regression will be carried out with each dependent variable and the intervention to analyze its effect on the different outcomes found. For the statistical tests, a 95 % confidence level will be considered, even if the p-values do not indicate a significant difference, we will report the effect size to give meaning and emphasize the power of the results [10].

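### Eligibility admits any knee operation at any stated interval, yet the planned regression names only the intervention; naming the T0 score, clinic, surgery type and days since surgery would be a cheap improvement

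*Protocol article*

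**What the plan says.** All references are to the protocol article.

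- **Inclusion and exclusion criteria.** The surgical criterion is the last part of "that can read and write; and (iv) have undergone knee surgery". Earlier surgery on the same knee and unconsolidated fractures are among the exclusions. No procedure is named and no interval since the operation is set.
- **Description of protocol.** Knee injuries are described as varied, "the most common of which are caused by ligaments, menisci, and cartilage".
- **Recruitment.** Patients come from clinics in one urban and one rural region. They are invited after a physiotherapy appointment, when recovery treatment has already begun. No limit in days or weeks is given.
- **Statistical methods.** The section plans a t-test or Mann-Whitney test, a two-factor ANOVA for group differences over the assessment times, and this: "A Multiple Linear Regression will be carried out with each dependent variable and the intervention to analyze its effect on the different outcomes found". No other predictor is named.
- **Sample size calculation.** The plan is "determining a minimum of 60 patients assuming an alpha error of 0.05", with power of 0.5 "and an effect size of 0,5". It then recruits 75 to allow for 20% loss.
- **Procedures and Evaluation.** Each outcome is measured at T0, at the end of the programme (T1) and six months later (T2).

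**The concern.** Patients recovering from different operations, or at different distances from the operation, may improve at different rates over six months. If so, part of the outcome variation is predictable from facts known at T0. A regression on the intervention alone leaves that part in the residual and widens the confidence interval for the programme effect. The trial is planned at a power of only 0.5, so it has little precision to spare.

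There is a second, smaller point. The model is called *multiple* but its further predictors are not named. Either it is unadjusted, or its covariates can still be chosen after the outcomes are known. Naming them now settles both.

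**Working it through.** **Inputs from the article:** alpha 0.05, power 0.5, effect size 0.5, minimum 60 patients, 20% loss, 75 recruited.

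**Assumptions:** two-sided test, 1:1 allocation (30 per arm analysed), and effect size read as a standardised mean difference. The article states none of these. R², the share of outcome variance that the covariates jointly explain, is not given either, so a range is used.

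**1. The plan's own figure.** By the normal approximation, n per arm = 2(z₀.₉₇₅ + z₀.₅)²/d² = 2(1.96 + 0)²/0.25 = 30.7. This rounds up to 31, or 62 in total, close to the stated 60. Then 60/0.8 = 75, as stated. By the noncentral t distribution, 32 per arm (64) would be needed, so the match rests on the approximation.

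**2. Unadjusted power at 30 per arm.** Noncentrality = 0.5 × √(30/2) = 1.936, with 58 degrees of freedom and critical value 2.002. Power is 0.478.

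**3. Adjusted power before any cost.** Replace d by 0.5/√(1 − R²). Power is 0.519, 0.567, 0.624 and 0.768 at R² = 0.1, 0.2, 0.3 and 0.5.

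**4. The cost of the covariates.** Four surgery types use 3 degrees of freedom. Days since surgery, the T0 score and clinic use 1 each (taking clinic as two levels), which makes 6. Residual degrees of freedom fall from 58 to 52 and the critical value becomes 2.007. Chance correlation between covariates and group inflates the variance by about 58/52 = 1.115. Noncentrality becomes 1.936/√(1.115 × (1 − R²)).

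| R² (assumed) | Noncentrality | Power after cost |
|---|---|---|
| 0 | 1.834 | 0.436 |
| 0.1 | 1.933 | 0.475 |
| 0.2 | 2.050 | 0.521 |
| 0.3 | 2.192 | 0.576 |
| 0.5 | 2.593 | 0.721 |

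Setting the adjusted power equal to 0.478 gives a break-even R² of about 0.11.

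**5. Chance imbalance, if allocation is random.** Take a surgery type carried by 30% or 50% of patients. The exact binomial probability that the arms differ by 15 percentage points or more, in either direction, is 0.204 or 0.245. If that type differed from the rest by 0.8 SD (assumed), a 15-point imbalance would shift the estimate by 0.15 × 0.8 = 0.12 SD. The standard error of the difference is √(2/30) = 0.26 SD, so the shift is under half of one standard error.

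**The case against.** - **The omission may not be one.** A reader might infer that the regression contains only the intervention. The article does not say so. The word *multiple* suggests further predictors, and a condensed article may leave the list to a fuller document. This stands: the supportable statement is that the regression *names* only the intervention.
- **Baseline may already be handled.** A reader might infer that differences between the groups go uncorrected. If T0 is a level of the time factor, the group-by-time term of the ANOVA deals with baseline differences in the outcome. This also stands, but that term does not separate recovery courses that differ by operation or by time since operation.
- **The case mix may be narrower in practice.** Patients are enrolled from physiotherapy clinics, and earlier surgery on the same knee is excluded. That limits repeat operations and probably the spread of timing. It sets no limit on procedure or interval.
- **The prognostic effect is unknown.** Nothing in the article supports calling the variation large. The R² values and the 0.8 SD are assumptions. If the covariates explain little, adjustment costs power, as the row for R² = 0 shows.
- **Imbalance is not bias.** Under random allocation the unadjusted test already allows for chance imbalance in its type I error, so the argument for adjustment is precision. The text at hand does not state how the groups are formed. If they were not formed at random, imbalance could be systematic and adjustment would matter more.
- **Adjustment does not cure planning at a power of 0.5.** This is correct, and it is a separate matter.

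**Conclusion.** The point holds as a cheap improvement, not as an error that invalidates the analysis. Eligibility is broad in procedure and timing. The one regression that the article states does not, as written, use the T0 score, the clinic or the surgical case mix.

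The size depends on an R² that the article does not give. From an unadjusted power of 0.48, the proposed model gains essentially nothing at 10%, about 4 percentage points at 20%, about 10 at 30% and about 24 at 50%. These figures assume 30 per arm, a two-sided 0.05 test, a standardised difference of 0.5 and the full 6 degrees of freedom. R² refers to all the covariates together, including the T0 score, so it should not be credited to the two surgical items alone.

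**What to change.** Keep the eligibility criteria. Under Statistical methods, state the regression for each outcome at T1 and at T2 as: intervention, the T0 score of that outcome, clinic, type of surgery (ligament, meniscus, cartilage, other) and days since surgery. Name all of these before outcome data are seen, with a rule for collapsing sparse surgery types that does not look at outcomes. Count days since surgery at T0: the two programmes last four and six weeks, so time counted at T1 would partly reflect group.

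The T0 score and clinic are already at hand. The cost is two items from the clinical record, one amended sentence and up to 6 model degrees of freedom at about 60 evaluable patients. Collapsing surgery types reduces that number. The risk is a small loss of power if the covariates jointly explain less than about 10% of the variance.

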### Sample size calculation

GPower@ software was used to calculate the sample size, determining a minimum of 60 patients assuming an alpha error of 0.05, a sample power of 0,5 (Power = 1-β err prob), and an effect size of 0,5. Anticipating a potential loss of 20% in follow-up due to the period required for the program (with evaluation at 6 months) and based on the numbers from each of the centers, a total of 75 patients will be recruited.

The experimental group will complete the rehabilitation program, in which the intervention takes place in five sessions per week over 4 weeks, with the physiotherapist supervising all the sessions (Fig. 1).

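### The stated inputs (alpha 0.05, power 0.5, effect size 0.5) do not return 60 patients under the named group-comparison tests, and the design has only about an even chance of detecting its planned effect

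*Protocol article*

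**What the plan says.** Under Sample size calculation, the Protocol article describes the calculation as "determining a minimum of 60 patients assuming an alpha error of 0.05, a sample power of 0,5", where power is defined as 1-β, together with "an effect size of 0,5". The minimum of 60 becomes 75 recruited after allowing for 20% loss. The section does not name the test, say whether it is one- or two-sided, identify the effect size as d or f, or give the allocation. The specifications table describes a design "with an experimental group and a control group".

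Statistical methods names Student's t-test for independent measures, Mann-Whitney U when normality fails, a two-factor ANOVA across assessment times, and multiple linear regression. It adds that "a 95 % confidence level will be considered". For results without a significant difference it says "we will report the effect size to give meaning and emphasize the power of the results".

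**The concern.** A software minimum is an exact number, so the stated inputs should return it under some natural choice of test. If none does, a reader cannot tell which input is wrong.

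Power of 0.5 is also an unusual target. The text defines it as 1-β, so a misprint cannot simply be presumed. If it is a slip for a conventional value, 60 may be far too few. If it is meant, the trial is planned to have a one-in-two chance of missing the effect it was sized for. In either case the paragraph gives a misleading picture of what a null result would mean. The Statistical methods sentence adds to this by describing an observed effect size as a way to emphasise power, which it cannot show.

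**Working it through.** **Inputs from the Protocol article.** Alpha 0.05, power 0.5, effect size 0.5, minimum 60, loss 20%, recruited 75 (Sample size calculation). The tests come from Statistical methods.

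**Assumptions.** 1:1 allocation (30 per group at 60). Effect size is Cohen's d unless stated otherwise. Two-sided is the base case, which fits the 95% confidence level.

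**1. Loss allowance.** 60 / (1 − 0.20) = 75. This step is correct.

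**2. Normal approximation, two-sided.** n per group = 2(z₀.₉₇₅ + z₀.₅)² / d² = 2(1.96 + 0)² / 0.25 = 30.7, so 31 per group and 62 in total. At 30 per group, d√(n/2) = 0.5 × √15 = 1.936, and power = Φ(1.936 − 1.960) = 0.491. This is the closest approach to the plan's figure, 2 patients away.

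**3. Exact two-sided t-test.** Noncentral t, noncentrality 1.936, 58 df, critical value 2.002. Power at 30 per group is 0.478. Power 0.5 needs 31.7, so 32 per group and 64 in total (power 0.504). With 20% loss, 64 / 0.8 = 80 recruited.

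**4. Other readings.**

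| Reading | Total N for power 0.5 | Power at N = 60 |
|---|---|---|
| Two-sided t, d = 0.5, 1:1 | 64 | 0.478 |
| Mann-Whitney, two-sided, efficiency 3/π | 68 (31.7 / 0.955 = 33.2, so 34 per group) | 0.460 |
| One-sided t, d = 0.5 | 46 (22.3, so 23 per group) | 0.606 |
| Two-sided t, 2:1 allocation | about 71 | 0.435 |
| F-test, two groups, f = 0.5 (equivalent to d = 1) | 18 | 0.968 |

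None returns 60. A repeated-measures ANOVA also needs a correlation between assessments, which the article does not give. With f = 0.5 and assumed correlations of 0.3 to 0.7, power for the group effect at 60 patients is at least 0.989, far from 0.5.

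**5. If the printed power is a slip.** With d = 0.5 (two-sided t), power 0.8 needs 64 per group, 128 in total, and power 0.95 needs 210. With f = 0.5 and two groups, 0.8 needs 34 and 0.95 needs 54. None of these is 60 either.

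**6. What the design delivers (two-sided t, d = 0.5).**
- 60 evaluable: power 0.478.
- All 75 evaluable (37 and 38): power 0.570.
- Effect detectable with 80% power at 60 evaluable: d = 0.736, about 0.74.
- Smallest observed d that reaches significance at 60: 2.002 × √(2/30) = 0.517, which is above the planned 0.5.
- The same 0.517 is the approximate half-width of the 95% interval in SD units. An observed d of 0.4 would give about −0.12 to 0.92, which includes both no effect and the planned effect.

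**The case against.** A reader might infer that 60 patients flatly fail to deliver the stated power. The documents do not support that. The shortfall is about 2 points, or 4 patients. It almost disappears under the normal approximation (62 patients, power 0.491) and reverses under a one-sided test (0.606) or f = 0.5 (0.968). The article does not say which applies, and a condensed article may leave that to a fuller protocol. This objection stands in full against the unconditional claim.

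It is equally tempting to say that the trial will miss its planned effect more often than it finds it. That needs no more than about 60 evaluable patients. The 20% loss is linked to the 6-month evaluation, so more may be available just after the intervention. From 64 evaluable upwards, t-test power passes 0.5. About even is as far as the figures go.

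The sentence in Statistical methods might be taken as a plan for post-hoc power claims. It commits only to reporting effect sizes, which is good practice, and plans no such calculation. Only the stated purpose is wrong.

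Analysis could also gain power from the regression if it were adjusted for baseline. The article does not specify that adjustment and gives no correlation, so no power figure for it is offered here.

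The objection does not remove the main point. The target of 0.5 is printed and defined in the text, and the stated inputs do not return 60 on any of the readings tabulated.

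**Conclusion.** The point holds in a limited form. As printed, the 60 cannot be reproduced from its own inputs with the t-test or Mann-Whitney, and the metric, sidedness and test needed to resolve the matter are not given. The mismatch itself is minor on the two-sided reading.

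The firm part is the level of power: about 50% for the planned effect, between 0.48 and 0.57 depending on retention between 60 and 75, with 80% reached only for an effect about half as large again as planned (0.74 / 0.5 = 1.48). This rests on a two-sided t-test, d = 0.5 and equal groups. A one-sided test would raise power, while 2:1 allocation or Mann-Whitney would lower it. Under f = 0.5 the design would be well powered, but the stated power of 0.5 would then be far from what 60 patients give. The inputs and output therefore need reconciling on every reading.

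**What to change.** In Sample size calculation, state the test, sidedness, effect-size metric and allocation actually entered, and correct whichever figure does not fit. If the two-sided t-test with d was intended, suitable wording is: *60 evaluable patients (30 per group) give about 48% power for d = 0.5 and 80% power for d = 0.74, two-sided t-test, alpha 0.05.* If 0.5 was a slip for another power, say so and give the power that 60 patients provide. Any power quoted for a baseline-adjusted analysis should name its assumed correlation.

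As a minor companion change in Statistical methods, keep the commitment to report effect sizes but replace the purpose clause with: *the between-group difference will be reported with its 95% confidence interval; a non-significant result will be read neither as evidence of an effect nor as evidence of equality.*

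The cost is wording only. Recruitment stays at 75, and the stated figures become slightly less favourable.

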**Fig. 1 fig0001:**
[figure not shown]
Program schedule.

### Recruitment

Participants will be recruited from rehabilitation clinics in an urban region (Oeiras-Portugal) and a rural region (Portel-Portugal), where they have started a recovery program. They will be invited to take part in the study immediately after their physiotherapist appointment, will be informed about the aims of the study and asked for informed consent (already approved by the Ethics Committee of the National School of Public Health - NOVA University of Lisbon).

### Procedures

Participants will complete the intervention described in Table 1, based on the updated Journal of Orthopaedic and Sports Physical Therapy (JOSPT) guidelines for knee injuries [3].

**Table 1 tbl0001:** Knee treatment intervention protocol.

Interventions	week			
	1	2	3	4
Massage	x	x	x	x
Passive Mobilization	x	x		
Active Mobilization	x	x	x	x
Neuromuscular Electrical Stimulation (NMES)	x	x	x	x
Proprioceptive Training		x	x	x
Isometric Exercises: Quadriceps; Vastus Medialis Oblique Muscle (VMO); Hip Adduction	x	x		
Isotonic Exercises: Gastrocnemius	x	x		
Isotonic Exercises: Quadriceps; Hip extension; Hip adduction; Hip abduction; Hamstrings	x	x	x	x
Standing Isotonic Gastrocnemius Exercises		x	x	x
Wall Slide 0° to 30°		x		
Wall Slide 0° to 45°			x	
Wall Slide 0° to 90°				x
Static Ergometer		x	x	x
Treadmill Progression: gait>run				x
Single Leg Vertical Jump				x
Specific Sport Exercises				x
Lower Limbs Stretching	x	x	x	x
Cryotherapy	x	x		

Initial data will be collected at baseline (T0), the intervention will then take place, an evaluation will be carried out shortly after the end of the intervention (T1) and the final evaluation will be carried out 6 months after the end of the intervention (T2). The following PROMs will be applied before and after the intervention:-The “**EQ-5D-5L**” instrument comprises five dimensions, each describing a different aspect of health: Mobility, Self-care, Usual activities, Pain/discomfort, and Anxiety/depression. Each dimension has five response levels: no problems, slight problems, moderate problems, severe problems, unable to/extreme problems. The visual analogue scale of this questionnaire has a score of 0–100. Higher scores mean better quality of life and lower scores indicate lower quality of life [4];-The “**HADS**” instrument, developed to detect symptoms of anxiety and depression, is made of 14 items, subdivided into two subscales - Anxiety and Depression, with a maximum score of 21 points for each subscale. The subscale scores can be calculated separately or together, with each item scored from 0 (absent) to 3 (extremely present) [5];-The “**BREQ2**” instrument has 19 items with five response options on a Likert scale, where 0 is "not true for me" and 4 is "often true for me" to assess the constructs of: amotivation, external regulation, introjected, identified and intrinsic motivation. The results can vary from 24 (lowest self-determination) to 20 (highest self-determination) [6].

